### Participant timeline {13}

All patients with EMS will be screened with history taking, laboratory tests, physical examinations, and ultrasonography. After admission for operation, written and informed consent will be obtained from patients who agree to enroll in the trial. Then, the subjects will be randomly assigned to one of the two groups. All patients will get routine hospital care with additional tests of serum hemoglobin and AMH levels and transvaginal/transrectal ultrasonography 2 days after surgery. These tests will be repeated at 3 months and 12 months after surgery. Supplementary Table 1 shows the schedule of enrollment, interventions, and assessments for participants.

### Sample size {14}

The number of participants is determined on the basis of the decline ratio of serum AMH levels 3 months after surgery with a significance level of 2.5% and the test power of 80%. For patients with ovarian EMS treated with laparoscopic suturing, the decline ratio of serum AMH levels 3 months after surgery has been reported to be 24.6% (interquartile range [IQR], 11.6–37.0) in the previous study [14]. From IQR and with the assumption of a normal distribution, standard deviation (SD) was calculated to be 18.81, where SD = IQR/1.349. Although the information on confidence intervals from relevant trials is required for determining the non-inferior margin, there appears no available study for confidence intervals. In one study on the comparison of the preservation of ovarian reserve between hemostatic suturing and electrocoagulation, it was reported that there was no significant difference between the two groups with respect to a reduction rate of serum AMH 3 months after surgery (suturing group 44% ± 28% vs. electrocauterization group 58% ± 24%, *p* = 0.15) [15]. Based on the 14% difference in the rate, we have calculated appropriate numbers of participants for the non-inferior margin from 8 to 14%. The smaller the non-inferior margin, the larger the sample size. Therefore, we set the non-inferior margin at 12% for the primary outcome, which will not be applied for the secondary outcomes because of a lack of relevant references. For the statistical test on non-inferiority with a mean difference of 0, the value for the sample size (*n* = 80) is available with SD of 18.81, and a non-inferior margin of 12% between the two groups, suggesting that the number of participants of each group is estimated to be 40. Supposed that the dropout rate is 10%, the number of participants should be 90 (45 per group).

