**Discussion:**

We expect that the protective effect for the ovarian reserve and hemostasis may be comparable between the two methods, suggesting that a hemostatic agent may be preferred considering that it is easy to use during laparoscopic ovarian cystectomy.

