### Objectives {7}

This study aims to evaluate the protective effect for preserving the ovarian reserve and hemostasis between a hemostatic agent and suturing during laparoscopic ovarian cystectomy for patients with ovarian EMS. Thus, we will estimate the reduction rate of serum AMH levels for the ovarian reserve, the time required for complete hemostasis, andhemoglobin levels with estimated blood loss for hemostasis between the two methods.

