### Interventions

#### Explanation for the choice of comparators {6b}

In laparoscopic ovarian cystectomy, not only to control bleeding, but it is also important to preserve the ovarian reserve. There are several methods to control bleeding during the operation, such as bipolar electrocoagulation, suturing, and the use of a hemostatic sealant. However, there are insufficient data to compare the effect to preserve the ovarian reserve and hemostasis between a hemostatic agent and laparoscopic suturing for patients with ovarian EMS. Therefore, this study is designed to show the similar effect of a hemostatic agent compared to laparoscopic suturing for the preservation of the ovarian reserve and hemostasis during laparoscopic ovarian cystectomy.

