## Statistical methods

### Statistical methods for primary and secondary outcomes {20a}

Both per-protocol (PP) and intention-to-treat (ITT) populations will be analyzed in two groups. The result will be regarded as valid when the experimental group is not inferior to the control group for the primary outcome, preservation of the ovarian reserve, in both analyzing methods. Serum AMH levels will be analyzed by using the Student *t* or Mann-Whitney *U* tests and repeated measure ANOVA. For secondary endpoints, variables will be analyzed by using the chi-square or Fisher’s exact test for categorical data and the Student *t* or Mann-Whitney *U* test for numerical data. *p* value < 0.05 is considered statistically significant.

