Based on these results of the PRAHA trial, we aimed to enroll only patients with ovarian EMS for comparing the protective effect for the ovarian reserve and hemostasis between laparoscopic suturing and the use of a hemostatic agent in the PRAHA-2 trial. Although laparoscopic suturing can result in mechanical damage to the normal ovarian tissue and increased intra-ovarian pressure in ischemic regions, relevant trials comparing the ovarian reserve and hemostasis after laparoscopic ovarian cystectomy between suturing and bipolar electrocoagulation have reported that bipolar electrocoagulation may have a similar effect for hemostasis to suturing, but further reduce the ovarian reserve [13, 22]. When we consume that the hemostatic effect may be similar between suturing and a hemostatic agent, we can expect that suturing can be less beneficial than the use of a hemostatic agent due to the potential of ischemic damage to the ovarian tissue after suturing. Nevertheless, a recent systematic review suggested that suturing for hemostasis may be recommended compared to bipolar electrocoagulation and the use of a hemostatic agent based on the results of previous trials, suggesting that additional hemostasis using bipolar electrocoagulation may be more required during the use of a hemostatic agent than during suture [23]. Most importantly, there is no well-designed trial for comparing the protective effect for the ovarian reserve and hemostasis between suturing and the use of a hemostatic agent for patients with ovarian EMS. Since we estimated the sample size as logically as possible based on the existing research results, we believe that the PRAHA-2 trial will show the definite comparative results between laparoscopic suturing and a hemostatic agent, which will be helpful for preserving the ovarian reserve with effective hemostasis during laparoscopic ovarian cystectomy for patients with ovarian EMS.

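### Similar hemostasis is a stated design aim, but only AMH has a margin and hemostasis is tested only for difference, so the plan has no valid route to that conclusion

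*Protocol article*

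**What the plan says.** **Aim.** Explanation for the choice of comparators {6b} says the study is "designed to show the similar effect of a hemostatic agent compared to laparoscopic suturing", and the sentence goes on to name both ovarian reserve and hemostasis. Objectives {7} pairs them too: the trial is to "evaluate the protective effect for preserving the ovarian reserve and hemostasis between a hemostatic agent and suturing".

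**Expected conclusion.** The Discussion paragraph of the Abstract reads: "We expect that the protective effect for the ovarian reserve and hemostasis may be comparable between the two methods". It goes on to suggest that the agent may then be preferred because it is easy to use. Background and rationale {6a} ends by saying that, if similar efficacy is shown, the agent may be an alternative to suturing for both purposes.

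**Outcomes.** The primary outcome is the AMH decline ratio at 12 weeks. Hemostasis is measured only by secondary outcomes: time to complete hemostasis, success within 10 minutes, blood loss, hemoglobin and transfusion.

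**Criterion.** Sample size {14} sets a 12% non-inferiority margin for the primary outcome, "which will not be applied for the secondary outcomes because of a lack of relevant references".

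**Analysis.** Statistical methods for primary and secondary outcomes {20a} confines the non-inferiority rule to the primary outcome. It then says: "For secondary endpoints, variables will be analyzed by using the chi-square or Fisher’s exact test for categorical data", with the Student t or Mann-Whitney U test for numerical data and p < 0.05 as the threshold.

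**The concern.** A statement that two methods are similar or comparable needs a criterion for how far apart they may be, or at least an interval that shows which differences the data exclude. The plan gives hemostasis neither. A significant difference test would contradict similarity; a non-significant one would leave the question open. Neither result delivers the conclusion that the article says the study is designed to reach.

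The direction that matters is poorer hemostasis with the agent. The article's main Discussion cites a systematic review suggesting that "additional hemostasis using bipolar electrocoagulation may be more required during the use of a hemostatic agent than during suture". That is the possibility a claim of comparable hemostasis would have to address, and in a trial of this size a difference test can easily miss it. At stake is the hemostasis half of the stated aim; the AMH conclusion is not affected.

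**Working it through.** **1. What the sample size covers.** Inputs from Sample size {14}: margin 12, SD 18.81, true difference 0, significance level 2.5% (taken as one-sided), power 80%.

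n per arm = 2 × (1.960 + 0.842)² × 18.81² / 12² ≈ 38.6, so 39 per arm. With the t distribution, 39 per arm gives power 0.794 and 40 per arm gives 0.804, hence 40 per arm and 80 in total. Dropout: 40 / 0.9 = 44.4, so 45 per arm and 90 in total. The article's figures reproduce. They rest on AMH alone; no hemostasis outcome enters.

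**2. Aim against analysis.**

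| | Ovarian reserve (AMH) | Hemostasis |
|---|---|---|
| Named in the design aim {6b} | yes | yes |
| Named in the expected conclusion (Abstract, {6a}) | yes | yes |
| Non-inferiority margin {14} | 12 points | none |
| Decision rule {20a} | not inferior in both PP and ITT | none |
| Planned analysis {20a} | t or Mann-Whitney, repeated-measures ANOVA | difference tests, p < 0.05 |

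**3. What the difference test can show for 10-minute success.** The article gives no success rates, so all rates here are assumptions. The probability of p < 0.05 (two-sided) is the sum, over all pairs of success counts, of Binomial(n, p₁) × Binomial(n, p₂) for the pairs at which the test rejects. Chi-square is without continuity correction.

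| Assumed success, suturing vs agent | n per arm | p < 0.05, Fisher | p < 0.05, chi-square | p ≥ 0.05 (chi-square to Fisher) |
|---|---|---|---|---|
| 90% vs 75% | 45 | 0.362 | 0.489 | 51% to 64% |
| 90% vs 80% | 45 | 0.179 | 0.277 | 72% to 82% |
| 90% vs 70% | 45 | 0.575 | 0.694 | 31% to 43% |
| 90% vs 75% | 40 | 0.334 | 0.436 | 56% to 67% |
| 90% vs 80% | 40 | 0.162 | 0.247 | 75% to 84% |

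**4. Precision.** With 90% success in both arms, the half-width of the 95% confidence interval for the difference is 1.96 × √(2 × 0.9 × 0.1 / 45) = 0.124, about 12 points. With 40 per arm it is 0.131, about 13 points.

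**5. Continuous outcomes.** For an outcome such as time to hemostasis, a two-sided t test with 45 per arm has power of about 65% at 0.5 SD, 80% at 0.6 SD and 91% at 0.7 SD (effect sizes assumed). These outcomes are more sensitive than the binary one. Even so, at 0.5 SD about 35% of trials would give p ≥ 0.05.

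**6. Would a formal test fit the present size?** With one-sided 2.5%, 80% power and 90% success in both arms, non-inferiority on 10-minute success needs 142, 63 or 36 per arm for margins of 10, 15 or 20 points. Only the widest fits within 40 to 45 per arm, so reporting intervals is more realistic than adding a hemostasis margin.

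**The case against.** The strongest reply is that nothing in the article says a p-value of 0.05 or more on hemostasis will be read as similarity. A reader might infer such a rule, because no other route to a conclusion of comparable hemostasis is planned, but the text does not contain it. The validity rule in {20a} is confined to the primary outcome, and {14} openly declines a margin for the secondary outcomes and gives a reason. The Abstract's statement is a hedged expectation. In {6a}, the sentence on preferring the agent is conditioned on ovarian reserve alone; hemostasis enters only in the closing sentence about an alternative. All this is correct, and the point does not rest on a written misreading rule. It rests on the design aim in {6b}, which covers hemostasis without qualification.

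Second, secondary outcomes need no margin, and an article may leave intervals to a fuller document. Both are fair. Omitting a margin is not the fault; pairing that omission with a claim of similarity is. Because the article itself fixes the difference tests and withholds the margin, an analysis plan that followed it would not resolve the mismatch.

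Third, the calculation depends on assumed rates and on one binary outcome, while Objectives {7} names time to hemostasis, hemoglobin and blood loss. This stands as a limit on size. A reader might infer that a relevant deficit would usually be missed. That does not hold in general: under chi-square, 90% against 75% is close to a coin flip, and 90% against 70% would be detected more often than not.

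Fourth, a reader might extend the criticism to the word similar as applied to AMH. The article does not support that as an analysis fault: the rule in {20a} is already one of non-inferiority, so for AMH it is only a matter of wording.

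**Conclusion.** The mismatch stands. The article says the trial is designed to show a similar effect on hemostasis as well as on ovarian reserve, yet only AMH has a margin and a decision rule, and hemostasis is tested only for difference. No result of those tests would establish similar or comparable hemostasis.

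The illustration shows that this is more than a formality: at 45 per arm, a 10-point deficit from 90% gives a non-significant result in about 72% to 82% of trials, and a 15-point deficit in about 51% to 64%. These figures rest on assumed success rates, two-sided tests at 0.05 and full data at 45 per arm, and they concern the binary outcome only. The primary AMH analysis and its sample size are unaffected. The point should be corrected, but it does not threaten the trial's main conclusion.

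**What to change.** - In {20a}, state that success within 10 minutes, time to hemostasis and blood loss will be reported as between-arm differences with two-sided 95% confidence intervals.
- In the same section, state that p ≥ 0.05 on a hemostasis outcome will not be taken as evidence that the methods are comparable.
- Limit the confirmatory claim to AMH decline not being worse by more than the stated margin, and describe hemostasis by its estimates and intervals.
- Align the hemostasis wording in the Abstract's Discussion paragraph, Background and rationale {6a} and Explanation for the choice of comparators {6b} with that claim.

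The cost is a few sentences and routine intervals. Sample size, conduct and data collection do not change. The downside is a narrower claim: the trial could no longer announce comparable hemostasis, only show which differences its data exclude.

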### Recruitment {15}

We will enroll patients with unilateral or bilateral ovarian EMS who are to undergo laparoscopic ovarian cystectomy at Seoul National University Hospital and Dongguk University Hospital in the Republic of Korea. For achieving adequate participant enrollment to reach the target sample size, more institutions will be considered to be included during this trial.

### Assignment of interventions: allocation

#### Sequence generation {16a}

A randomization table will be made by using a reproducible website program (http://randomization.com). The table will be managed by one staff who is a gynecologist but not associated with this trial.

#### Concealment mechanism {16b}

Eligible patients will be allocated to receive the designated intervention during operation. However, she will get to know her allocation after the operation. On the other hand, the operator will be unblinded just before surgery to conduct the appropriate intervention for the patient. Actually, this current study is open-labeled.

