## Abstract

**Background:**

Endometriosis (EMS) can be implanted everywhere, especially in pelvic organs. EMS can be asymptomatic, but it can result in pelvic pain and infertility by inducing local inflammation and pelvic adhesion. The prevalence of EMS is about 10% in reproductive-age women and higher in women with pelvic pain or infertility. For young patients with ovarian EMS, laparoscopic ovarian cystectomy is effective in relieving pelvic pain and preventing local recurrence. However, there is a concern that the ovarian reserve would decrease after the operation because of the removal of a part of the normal ovarian tissue and thermal damage during hemostasis, which depends on the types of hemostasis such as bipolar electrocoagulation, suturing, and the use of a hemostatic agent. In this study, we aim to evaluate the protective effect for the ovarian reserve and hemostasis between a hemostatic agent and suturing during laparoscopic ovarian cystectomy for patients with ovarian EMS.

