## Introduction

### Background and rationale {6a}

Endometriosis (EMS) is a condition that endometrial tissues are present outside the uterus. The most common sites of EMS are pelvic organs and peritoneum, but it can sometimes be seen at distant sites. The prevalence of EMS is about 10% in reproductive women, and it is higher in women with dysmenorrhea or infertility (17–44%) [1]. Although some women with EMS have no symptoms, a significant number of women with EMS have several symptoms such as dysmenorrhea, dyspareunia, and chronic pelvic pain and suffer from relevant infertility and cancer because of local inflammation and adhesion by EMS in the pelvic cavity [2].

Up to now, diagnostic laparoscopy is the gold standard for histologic confirmation of EMS, but medical treatment can be considered when ovarian EMS and deep infiltrating nodules are identified on imaging studies such as ultrasonography and magnetic resonance imaging. The treatment of EMS is individualized in consideration of age, the severity of symptoms, birth plan, and so on. Initially, medical treatment using nonsteroidal anti-inflammatory drugs and hormonal agents such as oral contraceptives, progestins, and gonadotropin-releasing hormone agonists can be considered [3]. However, surgical resection of deep infiltrating nodules or ovarian cystectomy should be conducted to relieve symptoms and improve the pregnancy rate [4, 5].

Nevertheless, surgical techniques for ovarian cystectomy can affect the remaining ovarian reserve after surgery because damage to the normal ovarian tissues depends on the proficiency in surgery to leave the normal ovarian tissue as much as possible and the methods for bleeding control. Sometimes the serum level of anti-Müllerian hormone (AMH) is measured before and after surgery to estimate the ovarian reserve. In young women, especially subfertile women who want to have a baby, the serum AMH level is a valuable predictor of reproductive potential [6]. In terms of bleeding control during laparoscopic ovarian cystectomy, bipolar electrocoagulation is a traditional and easy method, but it is hard to avoid thermal damage to the normal ovarian tissue. On the other hand, suture of the ovarian tissue can induce hemostasis effectively while avoiding thermal damage. However, it can lead to ischemic damage to the ovarian tissue due to excessive suture [7].

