### Trial design {8}

This is an open-label, parallel-group, randomized controlled, non-inferiority trial. Participants with ovarian EMS will be randomly assigned to the experimental (hemostatic agent) and control (suturing) groups at a 1:1 ratio. After surgical treatment of ovarian EMS, we will check the serum AMH and hemoglobin levels and ovarian volumes measured by transvaginal or transrectal ultrasonography before surgery, after 2 days, after 3 months, and after 12 months. Figure 1 shows the schema of this study.

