### Intervention description {11a}

#### Control group (suturing group)

During operation, a barbed suture will be applied to the inner surface of the ovarian parenchyme where ovarian EMS was attached.

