#### Secondary outcome

The decline ratio of serum AMH levels 48 weeks after surgery.The time required for complete hemostasis: stop-watch will be operated right after finishing to remove EMS tissues. It will be measured how long the time has been spent on bleeding control.Success rates of hemostasis within 10 min: it will be evaluated whether hemostasis is finished within 10 min.Blood loss during operation: the volume of blood loss will be estimated by using a simple visual assessment technique referring to gauze count and irrigation bottle.Hemoglobin: 2 days, 12 weeks, and 48 weeks after surgery.Transfusion during admission.Adverse events associated with the operation, bleeding, or transfusion.Hospitalization (days).Operation time (min).

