#### Implementation {16c}

One designated staff will generate the allocation sequence by using the randomization program. After research investigators get informed consent from the subject, the staff will assign the patient to the determined group. The operator and other related investigators will be unblinded just before surgery to perform proper management.

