## Discussion

Up to now, relevant RCTs have shown no difference in the hemostatic effect between bipolar electrocoagulation and the use of a hemostatic agent [12, 14, 16–18]. This result means that the use of a hemostatic agent can reduce the frequency of use of bipolar electrocoagulation, thereby minimizing thermal damage to the ovarian tissues. In general, the ovarian reserve is defined as the number and quality of the ovarian follicles, and serum AMH levels are known to reflect the ovarian reserve well [9, 19]. Thus, some RCTs have suggested that the use of a hemostatic agent may be more beneficial for preserving the remaining ovarian reserve after laparoscopic ovarian cystectomy by showing that the decline ratio of serum AMH levels was lower in patients treated with a hemostatic agent than in those treated with bipolar electrocoagulation [12, 14, 17].

However, the PRAHA trial showed that the protective effect of a hemostatic agent was observed in only patients with ovarian EMS with no difference in the decline ratio of AMH between the two treatments in those with ovarian non-EMS. It means that the effort to minimize the removal of healthy ovarian tissue and the use of bipolar electrocoagulation can be helpful in preserving the ovarian reserve after laparoscopic ovarian cystectomy in most patients with ovarian cysts. However, we commonly conduct adhesiolysis sufficiently from tissues surrounding the lesion for patients with ovarian EMS. During the procedure, the vascular system within the ovarian cortex or surrounding the ovary can be injured, which can lead to lower serum AMH levels by an inadequate blood supply in the patients [20, 21].

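### The operator learns the arm just before surgery, so cyst excision, one named cause of ovarian reserve loss, is done unblinded although the arms differ only in the hemostasis that follows

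*Protocol article*

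**What the plan says.** Two sections fix when the arm is disclosed. Concealment mechanism {16b}: "the operator will be unblinded just before surgery to conduct the appropriate intervention for the patient". Implementation {16c}: "The operator and other related investigators will be unblinded just before surgery to perform proper management". Section {16b} also says that patients receive their allocated treatment during the operation. That describes when treatment is given and does not delay disclosure.

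The randomised step comes later. In the control group the barbed suture is "applied to the inner surface of the ovarian parenchyme where ovarian EMS was attached", so it can be placed only after the cyst has been removed. The hemostasis clock follows the same order: "stop-watch will be operated right after finishing to remove EMS tissues" (Secondary outcome).

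The protocol links the excision to ovarian reserve in three places:
- Abstract, Background: reserve may fall "because of the removal of a part of the normal ovarian tissue and thermal damage during hemostasis".
- Background and rationale {6a}: "damage to the normal ovarian tissues depends on the proficiency in surgery to leave the normal ovarian tissue as much as possible", alongside the method of bleeding control.
- Discussion: "the effort to minimize the removal of healthy ovarian tissue and the use of bipolar electrocoagulation can be helpful in preserving the ovarian reserve".

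The primary outcome is the proportional decline in serum AMH at 12 weeks.

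**The concern.** The reason given for early disclosure is that the operator must carry out the right intervention. That holds for hemostasis but not for excision, which is the same procedure in both arms. An operator who knows the arm may, without intending to, differ between arms in how much normal tissue is spared. AMH decline at 12 weeks reflects excision damage and hemostasis damage together, and no measure of the excision is among the listed outcomes. A difference in excision between arms would therefore be read as an effect of the hemostatic method.

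In a non-inferiority trial such a shift can act either way. It could make an inferior agent look acceptable, or make an equivalent agent fail.

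**Working it through.** **Order of events**

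| Step | Same in both arms? | Does the operator need the arm? | Is the arm known under the protocol? |
|---|---|---|---|
| Cyst excision | Yes | No | Yes ({16b}, {16c}) |
| Hemostasis | No | Yes | Yes |

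No section withholds the allocation until the first step is finished.

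**Inputs** (all from Sample size {14}): SD 18.81, margin 12 percentage points, true difference 0, significance level 2.5% (taken as one-sided), power 80%, 40 evaluable per arm, 10% dropout.

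**The plan's own figure.** Normal approximation: n = 2 × (1.960 + 0.842)² × 18.81² / 12² = 38.6, so 39 per arm. With the noncentral t distribution, power is 79.4% at 39 and 80.4% at 40, which gives the stated 40. Dropout: 40 / 0.90 = 44.4, so 45 per arm and 90 in total. The stated size is reproduced.

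**Sensitivity to an excision shift.** Let the difference be AMH decline on the agent minus decline on suturing, so positive values mean that the agent is worse. Standard error = 18.81 × √(2/40) = 4.206. Non-inferiority is declared when the upper 95% limit is below 12. If the apparent difference is d, the probability of declaring it is P(T > t₀.₉₇₅,₇₈), where T is noncentral t with 78 degrees of freedom and noncentrality (12 − d) / 4.206.

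- Shift b favouring the agent, true difference 12: d = 12 − b, noncentrality b / 4.206. The probability is the type I error.
- Shift b against the agent, true difference 0: d = b, noncentrality (12 − b) / 4.206. The probability is the power.

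Example, b = 2: the noncentrality is 2 / 4.206 = 0.476 for type I error and 10 / 4.206 = 2.378 for power.

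| Assumed shift b (points) | Type I error, shift favours agent | Power, shift against agent |
|---|---|---|
| 0 | 2.5% | 80.4% |
| 1 | 4.2% | 73.3% |
| 2 | 6.8% | 65.1% |
| 3 | 10.5% | 56.1% |
| 4 | 15.4% | 46.8% |
| 5 | 21.6% | 37.6% |

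The shifts are assumptions, because the documents give no figure for an operator effect. Any bias of the same size, whatever its source, would give the same results.

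**The case against.** The trial says plainly what it is: "This is an open-label, parallel-group, randomized controlled, non-inferiority trial". The surgeon cannot be blind to hemostasis. Other safeguards are in place: the randomisation table is held by a staff member outside the trial, assignment follows consent, and the primary outcome is a laboratory assay. No section is contradictory. These safeguards protect selection and measurement, but they do not reach the conduct of the excision. Open-label hemostasis is unavoidable; open-label excision is a choice.

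Other parts of the objection stand, and they limit what can be claimed:

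- A reader might infer that excision is the main driver of AMH loss. The protocol does not say so. It names hemostatic damage as well, and Background and rationale {6a} cites declines of 50.7% and 14.4% in endometriosis patients by hemostatic method.
- A reader might infer a bias in favour of the agent. The text is mixed. The Abstract expects comparability. The Discussion first expects suturing to be less beneficial and then cites a systematic review favouring suturing. Section {6a} speaks of proficiency, which does not by itself show that operators behave differently by arm.
- A reader might infer that early disclosure leads to exclusions after randomisation. No section provides for such exclusions, and both ITT and per-protocol analyses are required. When a patient is assigned is also a separate matter from when the operator is told. Leaving patients unrandomised on operative findings would mean changing Participant timeline {13} too, and that is not proposed here.
- A careless remedy would do harm. If the stop-watch ran while the team waited for the allocation, the wait would enter time to hemostasis and success within 10 minutes. Bilateral cases also need a rule, because treating the first ovary reveals the arm before the second is excised.

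**Conclusion.** The point holds as a low-cost design improvement. The excision is unblinded without need, and the protocol itself says that this step affects ovarian reserve. The result is an avoidable source of performance bias in the primary outcome, of unknown size and direction. If it amounted to 2 points, type I error would be 6.8% instead of 2.5%, or power would be about 65% instead of about 80%, depending on direction. These figures rest on the protocol's SD and margin, 40 evaluable per arm, normally distributed outcomes and an assumed shift. They show sensitivity and do not estimate the bias. No figure in the protocol is wrong on this account.

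Later release would not remove all performance bias. Applying the hemostatic method, and the decision to add electrocoagulation ({11b}), remain open-label.

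**What to change.** In {16b} and {16c}, state that the independent staff member releases the allocation to the operator only when cyst removal is complete, with both methods ready in theatre until then. For bilateral disease, release after both cysts are removed where the surgery allows; otherwise record which ovary was excised after release.

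Under Secondary outcome, protect the timing measures in one of two ways. Either start the stop-watch in the same way in both arms once the allocation has been disclosed, or keep the present start, record any wait and exclude it.

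Cost: theatre must be ready for either method, with a possible short wait or some unused product. The sample size stays at 40 evaluable and 45 randomised per arm. Trial status says that no patient had been recruited, with the first expected in January 2021, but the article appeared in July 2021. If enrolment has begun, the change needs IRB approval under {25}, and patients treated under the two release procedures should be identifiable in the data.
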